# Intravenous administration of adenosine triphosphate and phosphocreatine combined with fluoxetine in major depressive disorder: protocol for a randomized, double-blind, placebo-controlled pilot study

**DOI:** 10.1186/s13063-018-3115-4

**Published:** 2019-01-09

**Keywords:** Major depressive disorder, Adenosine triphosphate, Phosphocreatine, Fluoxetine, Fast-acting antidepressant, Randomized controlled trial

## Abstract

**Background:**

Major depressive disorder (MDD) is a common psychiatric disorder. With systematic antidepressant treatment, 50–75% of patients have a treatment response but require 4–6 weeks to have their symptoms alleviated. Therefore, researchers anticipate the development of novel fast-acting antidepressants. Previous studies have revealed that the decrease of bio-energetic metabolism may contribute to the occurrence of depression, while our team has found adenosine triphosphate (ATP) and phosphocreatine (PCr) to be fast-acting antidepressants in the depressed-animal model. ATP and PCr have already been widely prescribed clinically as energy supplements for cells. This will be the first clinical attempt of the intravenous administration of ATP and PCr combined with orally administered fluoxetine in MDD.

**Methods:**

This is a single-center, randomized, double-blind, placebo-controlled pilot study. A total of 42 patients will be divided randomly into three groups. Patients will receive an intravenous administration of ATP or PCr or saline twice daily combined with orally administered fluoxetine (20 mg/day) for the first 2 weeks and fluoxetine monotherapy for the following 4 weeks. Follow-up assessment will be completed at week 10. Feasibility outcomes will include percentages of patient eligibility, intention to use medication, willingness to participate, drug adherence, completion of the scheduled assessment, retention, drop-out, etc. Physical examination results, Side Effect Rating Scale, adverse events, results from blood tests, electroencephalogram, and electrocardiograph will be recorded for safety evaluation of the augmentation therapy. The trends of efficacy will be evaluated by the reduction rate of the Hamilton Depression Rating Scale, the mean change of the Clinical Global Impression Scale, and the Patients Health Questionaire-9 items.

**Discussion:**

In our study, ATP and PCr will be given by intravenous infusion. Thus patients will be hospitalized for the initial 2 weeks for safety concern. Hospitalization will be an impact factor for the recruitment, participation, drop-out, efficacy, results, etc. The evaluation of our feasibility outcomes, study setting, safety of augmentation therapy and possible efficacy trends among groups, will facilitate a full-scale trial design and sample size calculation.

**Trial registration:**

NCT03138681. Registered on 3 May 2017. First patient: 4 May 2017.

**Electronic supplementary material:**

The online version of this article (10.1186/s13063-018-3115-4) contains supplementary material, which is available to authorized users.

## Background

Major depressive disorder (MDD) is a long-lasting mental disturbance [1]. In China, the lifetime prevalence of MDD is approximately 3.3% [2]. It was accidentally observed that patients treated with reserpine, an antihypertension drug that depletes catecholamines, experienced depression, indicating a possible relationship between depletion of norepinephrine or 5-hydroxytryptamine in the brain and affective disorders [3]. Since then, the pharmacology of antidepressants (ADs) has generally been based on the classical monoaminergic hypothesis. To date, the selective serotonin reuptake inhibitors (SSRIs) have generally been selected when treating moderate to severe MDD.

Overall, with adequate first-line pharmacological treatment, 50–75% of patients experience symptom alleviation while the remaining exhibit no response to treatment. Generally, symptom alleviation requires 4–6 weeks after starting medication [4, 5]. Rapid response to treatment could improve patients’ adherence to regular drug intake and strengthen their confidence in overcoming depression, thus largely minimizing the risk of suicide. It may be true that the more progress made in the early treatment phase (first 2 weeks), the more favorable the future outcome that could be achieved [6]. Therefore, researchers anticipate the development of novel fast-acting ADs with minimal side effects.

One major strategy revolves around the modulation of the glutamatergic system. Ketamine, a non-competitive *N*-methyl-D-aspartate (NMDA) receptor antagonist, has attracted considerable attention. However, concern regarding potential drug abuse and psychotomimetic manifestations related to NMDA receptor blockage have prevented its broad clinical administration, particularly in individuals with a history of psychosis [7, 8].

Depression has been considered a syndrome rather than a single disease because even though patients exhibit the same clinical manifestations, the underlying etiology is highly heterogeneous [9]. We intend to identify an AD predominantly based on “the dysfunctional energy homeostasis hypothesis.”.

In multiple studies conducted on animal models of depression, several proteins involved in glycolysis and the tricarboxylic acid cycle, such as mannose-6-phosphate isomerase, glyceraldehyde-3-phosphate dehydrogenase, pyruvate kinase, and lactate dehydrogenase, as well as fumarate hydratase, aconitase, and the malic enzymes ME1 and ME2, have shown increased expression in cerebellar samples. Nevertheless, several metabolites related to energy metabolism (e.g., creatine, succinic acid, and glucose-1-phosphate) have been shown to be decreased both in the cerebellum and the prefrontal cortex (PFC), suggesting that energy deficiency with depression leads to compensatory upregulation of the enzymes associated with energy metabolism [10–12]. Positron emission tomography of patients with MDD, reflecting the blood flow and glucose metabolic rate in the brain, suggests reduced blood flow or glucose metabolism in the PFC, anterior cingulate cortex, and caudate nucleus. Conversely, in patients with bipolar disease, the reduced metabolic rate increases when transitioning from depression to the manic state [13]. The studies have demonstrated that altered metabolism in the PFC-limbic-striatal region could be normalized after alleviating clinical symptoms by both ADs treatment and non-pharmaceutical therapy [14, 15]. Bremner et al. found that when patients with MDD were in a remission state after SSRI treatment and underwent tryptophan-depletion procedures, 7 of 21 patients experienced a depressive relapse, accompanied by decreased or unchanged cerebral metabolism in the thalamus and middle frontal gyrus, whereas those without relapse displayed unaltered cerebral metabolism. Moreover, there is a significant inverse correlation between the metabolic state and the Hamilton Depression Rating Scale (HAMD) score [16].

Mitochondria are the powerhouses generating adenosine triphosphate (ATP). The tremendous energy demand of neuronal activities is provided by oxidative phosphorylation (OXPHOS) inside the mitochondria. The mitochondrial respiratory chain polypeptides are comprised of five respiratory chain enzyme complexes and two electron carriers, namely, coenzyme Q10 (CoQ10) and cytochrome.

Studies around MDD and mitochondrial activity or ATP synthesis have been conducted and proved to be relevant [17–22]. Approximately 54% of subjects diagnosed with a mitochondrial disease have comorbid MDD. “Mitochondrial cocktails” for the treatment of mitochondrial diseases, CoQ10/creatine in particular, also exert AD-like effects [23]. When treated with CoQ10 for 21 days, rats exposed to chronic restraint stress showed improvement both in the forced swimming test and the open-field test [24]. Clinically, a 4-week treatment of CoQ10 in geriatric bipolar depression resulted in a significant reduction in Montgomery Asberg Depression Rating Scale scores [25]. In an 8-week study of oral treatment with creatine, female adolescents with SSRI-resistant MDD showed a steady decrease in Children’s Depression Rating Scale-Revised (CDRS-R) scores and a significant increase in PCr in the brain on ^31^P magnetic resonance spectroscopy [26].

The limited reservoir of ATP in the brain demands a high re-synthesis rate to fuel vast energy requirements, accounting for approximately 20% of all energy production. In contrast, PCr, stored abundantly in the brain, transiently transfers high-energy phosphoryl bonds to form ATP through the activity of creatine kinase (CK). Thus, the continuous supply of the high-energy phosphoryl bonds by PCr appears to contribute to the dynamic equilibrium of ATP consumption and ATP synthesis [27].

In our preclinical studies, the ATP levels were significantly decreased in artificial cerebral spinal fluid, as well as in the interstitial fluid in the hippocampus and PFC, collected in susceptible mice but not in unsusceptible mice after chronic social-defeat stress. Lateral intracerebroventricular injection of ATP reduced total immobility time in the forced swimming test. Furthermore, 7-day intraperitoneal injections of ATP yielded AD-like effects to an extent similar to that of 28-day treatment with imipramine [28]. Additionally, intraperitoneal injection of PCr in the depressed rats at multiple dosages (31.25, 62.5, 125, 250 mg/kg) achieved remarkable AD effects, with 125 mg/kg PCr producing the best efficacy.

Together, the researches highlight a pivotal connection between reduced levels of ATP/PCr and depression. For this reason, we hypothesized that ATP and PCr may be potential fast-acting ADs in the treatment of MDD.

### Research objectives

Our pilot study aims to evaluate the feasibility and safety to conduct a full-scale trial of intravenous (IV) administration of ATP and PCr combined with orally administered fluoxetine to patients with moderate to severe MDD. The preliminary exploration of the AD effect of augmentation therapy over fluoxetine alone might allow us to obtain clinical insights beyond the results from preclinical animal studies.

### Trial design

This trial is designed as a single-center, randomized, double-blind, placebo-controlled clinical pilot study. An overall summary of our study process is shown in Fig. 1.

**Fig. 1 Fig1:**
[figure not shown]
Study process

## Methods: Participants, interventions, and outcomes

### Study setting

The study will be conducted at Zhujiang Hospital, Southern Medical University, Guangzhou, China. Patients will be assessed and hospitalized in the Neurology Department of the hospital.

### Eligibility criteria

#### Inclusion criteria

Patients eligible for the trial must meet all the following criteria:Firstly diagnosed with moderate to severe MDD, according to the *Diagnostic and Statistical Manual of Mental Disorders, Fifth Edition* (DSM-V)HAMD-24 total score ≥ 20Men and women aged between 18 and 65 years old; andVoluntary and written informed consent

#### Exclusion criteria

Patients meeting any of the following criteria will be excluded:Enrolled in any clinical trials in the previous 4 weeksPreviously diagnosed with MDD or a lifetime history of schizophreniaExperienced traumatic events in the previous 6 months and diagnosed with posttraumatic stress disorderPregnant, breastfeeding or planning to do soSevere physical diseases, such as severe dementia, aphasia, consciousness disturbance, and deafness, which could interfere with the judgment of depressionOther psychiatric disorders such as schizophreniform disorder, schizotypal (personality) disorder, and bipolar disorderSevere medical complications, such as hepatic, cardiac, pulmonary or renal dysfunctionNeurological disorders, e.g., epilepsy, acute stroke, multiple sclerosis, and malignant cerebral diseasesInflammatory diseases, including autoimmune disordersCurrent immunosuppression treatment or intake of antiarrhythmic, antidiabetic drugs or tryptophan agentsA history of substance-related or addictive disorders in the previous 6 months;Suicide attempts; andUnwillingness to participate in, or having difficulties, completing our study

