### Discontinuation criteria

If participants meet one of the following criteria, the study drugs will be withdrawn:■ The drug-related utilization ratio (number of actual tablets taken/number of planned tablets × 100%) is less than 80% or greater than 120%■ The risks in continuing to participate outweigh the benefits of our study due to the appearance or exacerbation of other diseases■ The aggravation of patients’ mental conditions, such as evolution into severe depression or manic episodes, a high risk of suicide attempts or suicidal acts, which would require altering medical treatment during the study period■ Severe side effects, severe adverse events; and■ Anticipated or accidental pregnancy■ Patients can leave our trial at any time for any reason■ The reason for withdrawing should be recorded on the Case Report Form (CRF)

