### Combination therapies

■ We prefer that enrolled subjects with mild sleep difficulties not receive any sleeping pills. Zolpidem, zopiclone or estazolam will be prescribed for patients with severe insomnia disorders■ Enrolled subjects with other physical illnesses will continue with their original treatment plan■ Considering the precision of our collected clinical outcome data, antipsychotics, ADs or mood stabilizers (e.g., sodium valproate, lithium carbonate) will not be allowed to be prescribed during the study period. Similarly, any drugs that could have interactions with our study drugs, such as antiarrhythmic or antidiabetic drugs or tryptophan, will not be administered either■ The participants’ treatment history and concomitant treatments should be recorded on the CRF

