**Table Taba:** 

Outcomes	
Recruitment period	
Feasibility outcomes	Our pilot study will be conducted in a general hospital. The difficulties while recruiting will be recorded and discussed in the final report. Regarding our study inclusion criteria, moderate to severe MDD patients with HAMD-24 ≥ 20 can be enrolled. Some of our eligible patients might be inclined to choose non-pharmacological treatment. The percentage of eligible patients refusing to participate in our study. Their reason will be recorded on the recruitment document and discussed in the final report. The percentage of eligible patients willing to participate in our study. Their reason will be recorded on the recruitment document and discussed in the final report
recruitment difficulties	
eligibility rate	
intention to use medication	
refusal rate	
participation rate	
Study period	
Feasibility outcomes	While hospitalized, the drug compliance will be guaranteed by bedside nurses. The assessment of adherence rate will follow schedule and their reason for not taking drugs will be recorded. (see Fig. 2). The percentage of enrolled patients withdrawn before completion of our study. Their reason will be recorded on the Case Report Form (CRF). If “yes,” the researcher should list the name/dosage/duration, and explain its reason for use on the CRF. After study period, the percentage of enrolled patients willing to receive medical advice from our clinical researcher. The occurrence rate of side effects or the adverse events. Test the conduction of our blinding method
adherence	
withdrawn	
concomitant therapy	
retention	
side effects/adverse events	
blinding	
Overall	
Feasibility outcomes	At any time of their participation, enrolled patients will be encouraged to report their suggestion or feeling to researcher. Also, they will receive a questionnaire questioning their perceptions toward the medical environment, treatment response, sense of security and suggestion while hospitalized. It will be recorded and discussed in final report. The appropriateness of the implementation of our study scheme and it will be discussed in final report
participation/hospitalization feedback	
study scheme	

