### Sample size

Considering that there are no previous studies from which to perform sample size calculation, and assuming drop-out rate less than 15%, we anticipate enrolling 14 patients per arm for a final sample size of at least 12 per arm [43]. Our collected data will aid in the calculation of the appropriate sample size for further large-scale study.

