### Recruitment

Patients with MDD will be recruited 1 year at Zhujiang Hospital, Southern Medical University, from May 2017 to April 2018. Posters for recruitment will be posted in the in-/out-patient buildings of the hospital and in the Mental Health Center of Southern Medical University. Network advertisements will be issued in public via social media circles. Generally, participants will contact us and set appointments prior to the screening. Afterward, two assigned physicians will evaluate whether participants are eligible for our study following the inclusion/exclusion criteria and will provide detailed information about our study if qualified; otherwise, relevant medical advice will be offered.

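### The suicide exclusion names attempts only, so a patient already at high suicide risk who has made no attempt is not clearly barred from entry

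*Protocol article*

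**What the plan says.** All places are in the protocol article.

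- **Exclusion criteria.** Meeting any listed item excludes a patient. The last two items, run together in the extracted text, read "Suicide attempts; andUnwillingness to participate in, or having difficulties, completing our study". The first carries no time window and mentions neither ideation, plan nor current risk. No other item names suicide.
- **Inclusion criteria.** Entry requires "Firstly diagnosed with moderate to severe MDD" and a HAMD-24 total of at least 20. There is no upper limit and no condition on suicide risk.
- **Recruitment.** At screening, "two assigned physicians will evaluate whether participants are eligible for our study following the inclusion/exclusion criteria". For people who do not qualify, "otherwise, relevant medical advice will be offered".
- **Discontinuation criteria.** Study drugs are withdrawn if the patient's mental condition worsens. One example given is "a high risk of suicide attempts or suicidal acts, which would require altering medical treatment during the study period".
- **Combination therapies.** In this section, "antipsychotics, ADs or mood stabilizers (e.g., sodium valproate, lithium carbonate) will not be allowed to be prescribed during the study period".
- **Interventions.** Every arm receives fluoxetine 20 mg daily for 6 weeks. Infusions of ATP, PCr or saline are given during the first 14 days, when patients are in hospital.

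**The concern.** The protocol itself separates suicidal acts from suicide risk. Its withdrawal rule counts high risk as a reason to stop study drugs and change treatment. Its entry rule counts only attempts. A patient whose high risk is already present at screening, and who has never made an attempt, falls between the two: the exclusion list does not name the condition, and the withdrawal rule is written for worsening during the study.

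Patient safety is at stake. Such a patient could be randomised to fixed-dose fluoxetine plus infusion or saline, with other psychotropic treatment of the kinds listed under Combination therapies prohibited while on study. The Study setting is a neurology department, and the Discussion allows some patients with supportive supervised housing to go home after day treatment.

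**Working it through.** No formula applies, and the plan states no figure on this point to reproduce. The check sets the rules side by side and follows one hypothetical patient through them: first-diagnosed severe MDD, HAMD-24 of 20 or more, no suicide attempt, high suicide risk on the day of screening.

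1. **Inclusion.** The patient meets the diagnosis and score criteria. Nothing there turns on suicide risk.
2. **Named exclusion.** The suicide item describes an act. Without a time window it can bar anyone with a past attempt, but this patient has made none, so it does not apply.
3. **Catch-all exclusion.** The last item bars people unwilling to take part or likely to struggle to complete the study. A physician may use it to refuse this patient. It does not mention suicide risk, so it permits refusal without requiring it, and two clinicians could decide the same case differently.
4. **Screening.** Two physicians decide eligibility against these same lists. That is a real safeguard, but the written criteria they apply are those in steps 1 to 3.
5. **Other mentions of suicide.** Apart from the withdrawal rule, the word appears only in the Background and Discussion, as context or a hoped-for benefit. Neither bars entry.
6. **After entry.** The regimen is fixed and the listed psychotropics are prohibited. If risk rises, the withdrawal rule applies and treatment can change. If risk was high from the start and has not risen, whether the rule applies depends on how strictly worsening is read.
7. **Mitigation.** There are 14 days of initial hospitalisation (Interventions), psychiatric status is checked at each evaluation (Safety outcome measures), and raters are experienced physicians with psychiatric training (Data management and monitoring). Fluoxetine continues for 6 − 2 = 4 weeks after the hospital period. All of these act after entry and do not settle who should enter.

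Result: no written rule requires that this patient be kept out, although one permits it.

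**The case against.** The strongest reply is that entry and withdrawal rules need not mirror each other. The withdrawal item is about change on treatment. It also names evolution into severe depression, yet severe MDD is admitted at entry, so a state that triggers withdrawal when it develops is not automatically a bar to starting. That stands, and it defeats a reading that someone might be tempted by, namely that the two rules contradict each other. They do not. It does not remove the gap: the authors chose to exclude on grounds of suicidality and drew that criterion around the act alone.

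A second reply is that a journal article condenses the protocol and that Fig. 2 is not available here. This also stands in part. A reader might infer that suicide risk is not assessed at screening; the article cannot show that. But the exclusion list is stated in full form, and the point concerns what that list covers.

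A third reply is that there are ample protections: active fluoxetine in every arm, a data monitoring committee charged with participants' interests, reporting of severe adverse events within 24 hours, and freedom to leave at any time. These reduce the harm, but they too operate after entry.

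A reader might also infer damage to the sample size or the feasibility results. The Sample size section says "assuming drop-out rate less than 15%, we anticipate enrolling 14 patients per arm for a final sample size of at least 12 per arm", which allows 14 − 12 = 2 losses per arm (2/14 = 14.3%). One early withdrawal would be 1/14 = 7.1% of an arm and 1/42 = 2.4 percentage points of the overall withdrawn percentage. Those figures hold for a withdrawal for any reason, and they assume that stopping study drugs counts as drop-out, so they say nothing about the size of this problem. The feasibility outcome is "The percentage of enrolled patients withdrawn before completion of our study", and both the outcomes table and the Discontinuation criteria require the reason to be recorded on the case report form. A withdrawal for suicide risk could therefore be identified and reported separately, and the outcome remains valid.

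Finally, the added criterion would still rest on the judgement of the same two physicians. That is true. The gain is that refusal becomes a stated requirement once they judge the risk to be high.

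**Conclusion.** The concern holds as a matter of patient safety. A patient at current high suicide risk with no attempt is not clearly excluded, while the protocol treats such risk as a reason to withdraw study drugs when it arises in the trial.

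The size cannot be given. The article reports no rate of such patients, and none is assumed here. Hospitalisation and physician screening make the gap smaller in practice than on paper. Sample size, power and the validity of the feasibility outcome are unaffected.

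The conclusion rests on reading the published exclusion list as the one that the screening physicians apply, which is what the Recruitment section says. It is a cheap and worthwhile improvement, not the correction of an error that undermines the trial.

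**What to change.** Add one item to the Exclusion criteria: *current high risk of suicide, as judged by the two screening physicians*. Refer patients excluded on this ground through the medical advice that the Recruitment section already provides for. The Discontinuation criteria can stay as they are, and no new instrument is needed.

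Under Protocol amendments, a change of this kind needs re-approval by the ethics committee and the sponsor before it takes effect. Trial status describes recruitment as ongoing. If the line is adopted before recruitment closes, the patients enrolled before and after it will have entered under different criteria, so the final report should give the amendment date and the number enrolled on each side of it. The remaining costs are a few more screen failures and slightly narrower generalisability.
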